## Abstract

**Background:**

There is still a large demand for effective treatments to delay disease deterioration in amyotrophic lateral sclerosis (ALS). Typical symptoms of ALS are considered “flaccidity syndrome” in traditional Chinese medicine (TCM). Huoling Shengji Granule (HLSJ) is a TCM formula used to treat flaccidity syndrome. Results of preclinical tests and a previous clinical study support HLSJ as a novel drug for ALS patients. This trial proposed to examine whether a 48-week course of HLSJ is effective and safe for ALS patients diagnosed with the Chinese medicine syndrome of spleen qi insufficiency and kidney yang deficiency.

**Methods and analysis:**

In this phase II, multicenter, randomized, double-blind, riluzole parallel-controlled, superiority-design study, eligible participants had the equal opportunity to be assigned to receive either HLSJ or riluzole randomly. Eleven specialized ALS centers in Mainland China will recruit 144 patients for this trial. The primary and secondary outcomes included the change in the ALSFRS-R score and the Rasch-Built Overall Amyotrophic Lateral Sclerosis Disability Scale (ROADS) from baseline to Week 48.

**Discussion:**

Here, we endeavored to evaluate TCM for ALS using a standard evidence-based approach for the first time. In addition, the ROADS, a self-report linear-weighted questionnaire, was selected as a secondary outcome measure. We expect to offer a new reference for the outcome evaluation of ALS trials.

**Clinical trial registration:**http://www.Chictr.org.cn, identifier ChiCTR2100044085.

## 1. Introduction

Up to now, only three interventions have received approval for the treatment of amyotrophic lateral sclerosis (ALS). Survival is prolonged by approximately 3 months with treatment of riluzole (Miller et al., 2012), and intravenous edaravone has been reported to be effective in slowing disease progression in a well-defined population in Japan (Writing Group, Edaravone (MCI-186) ALS 19 Study Group, 2017); however, the latter has not been verified in a real-world study in Europe (Witzel et al., 2022). AMX0035 increased the median survival by 6.5 months in a phase 2 trial (Paganoni et al., 2020). However, considering that the median survival in ALS is only 2–4 years (Tang and Fan, 2022), there is still a large demand to find more effective treatments to decelerate disease progression and prolong survival.

For ALS patients, the typical symptoms are muscle weakness, muscle atrophy, and difficulty in speaking or swallowing, which are considered “flaccidity syndrome” or “Wei Zheng” in traditional Chinese medicine (TCM). Based on the TCM theory, flaccidity syndrome is mainly induced by deficiency syndrome of the lung, spleen, liver, and kidney. Therefore, invigorating the spleen, replenishing qi, and nourishing the liver and kidney are considered as the principles of treatment, treating both the symptoms and root cause of disease (Zhu et al., 2017; Pan et al., 2021).

Huoling Shengji Granule (HLSJ) is a TCM formula for the treatment of Wei Zheng by tonifying qi, strengthening the spleen, warming the kidney, and invigorating yang. It consists of six herbs, with the proportion prescribed in a previous study (Radix Astragali: Epimedium herb: Radix Rehmanniae: Fructus Corni: Atractylodes macrocephala Koidz: Poria cocos = 6:5:5:4:3:3; Wu et al., 2021). The monarch herb, Radix Astragali, is used to invigorate middle-jiao energy and replenish qi; Epimedium herb is chosen as the monarch herb to unchoke the Governor Vessel and warm kidney-yang; as a minister herb of Radix Astragali, *Atractylodes macrocephala* Koidz facilitates tonifying qi of the stomach and spleen; Fructus Corni, the other minister herb of Epimedium Herb, promotes tonifying the liver, stomach, and kidney; *Poria cocos* can help tonify qi of the spleen without causing stagnation; and the cool nature of Radix Rehmanniae can regulate the heat property of the whole formula by nourishing yin (Zhou et al., 2018).

In the preclinical study, medium-dose HLSJ prolonged the mean survival and disease course of SOD1^G93A^ mice compared with the vehicle group with statistical significance, while the disease onset was not significantly delayed. In HLSJ group, motor neuron loss was prevented in the lumbar spinal cords in Nissl and TUNEL staining, and the aberrant expression of apoptosis-related proteins was corrected. In addition, HLSJ relieved atrophy of the gastrocnemius muscle and loss of the neuromuscular junction. HLSJ treatment also inhibited glial cell activation and suppressed the inflammatory response. Based on the above results, HLSJ has shown therapeutic effects in the animal model of ALS, which indicates HLSJ as a potential novel drug for ALS patients (Zhou et al., 2018).

In a previous clinical study, 64 patients with ALS were included and randomly divided into HLSJ decoction and riluzole groups, with a course of 12 weeks. No statistical differences were detected in changes in the Advanced Norris Scale score between the two groups. Compared to riluzole, the HLSJ decoction effectively decreased the symptom scores of the Chinese medicine syndrome. In consequence, HLSJ is worth further investigation as a promising drug for ALS (Sui et al., 2016).

The current phase II, multicenter, randomized, double-blind, riluzole parallel-controlled, superiority-design study is proposed to verify the efficacy and safety of HLSJ as a treatment for a 48-week period in ALS patients diagnosed with Chinese medicine syndrome of insufficiency of spleen qi and deficiency of kidney yang, compared with treatment with riluzole. Eligible participants had the equal opportunity to be assigned to receive either HLSJ or riluzole randomly.

## 2. Methods and analysis

### 2.1. Study setting

Eleven specialized ALS centers in Mainland China will recruit patients for this trial. All centers are members of the ALS Collaborative Group in China, awarded national or regional centers for the diagnosis and treatment of ALS, and all are able to conduct subject recruitment, management, and follow-up. Detailed information on the ALS centers, independent data monitoring committee, statistics units, contract research organization (CRO), site management organization, and sponsors is shown in Table 1.

**Table 1 tab1:** Institutions involved in the study.

Institution	City	Role and activity	Work package
Peking University Third Hospital	Beijing	Coordinating center	Convene expert committee, formulate the protocol and create the case report form (CRF) with statistics unit.
			Submit application to ethical committees.
			Train the protocol and outcomes measure.
			Present and disseminate the results with the permission of the sponsor.
			Enroll and follow-up the subjects.
The Second Hospital of Hebei Medical University	Shijiazhuang	Enrolling center	Participate in the seminar on protocol formulation and provide suggestions.
Henan Provinclal People’s Hosipital	Zhengzhou		Complete the training of the protocol and outcomes measure.
The First Affiliated Hosipital, Sun Yat-Sen University	Guangzhou		
			Enroll and follow-up at least four subjects.
Guangdong Province Traditional Chinese Medical Hospital	Guangzhou		
The Second Affiliated Hospital, Zhejiang University School of Medicine	Hangzhou		
West China Hospital of Sichuan University	Chengdu		
The First Affiliated Hospital of Xi’an Jiaotong University	Xi’an		
Fujian Medical University Union Hospital	Fuzhou		
The First Affiliated Hospital of Harbin Medical University	Harbin		
Renmin Hospital of Wuhan University	Wuhan		
/	/	Independent Data Monitoring Committee	Safety monitoring, efficacy monitoring, operational quality control, and suggestions for adjustment of trial design.
			Conduct an interim analysis and assess the risks and benefits for the subjects.
			Make a key recommendation whether the trial continues.
Wuhan Zhizhi Medical and Pharmaceutical Technology Co., Ltd.	Wuhan	Statistics unit	Participate in the design of the protocol and statistical plans.
			Establishment and management of Electronic Data Capture System and central randomization system.
			Blind codes.
			Statistical analysis.

### 2.2. Participants

The trial will enroll patients diagnosed with ALS according to the revised El Escorial criteria (Brooks et al., 2000) and the criteria of insufficiency of spleen qi and deficiency of kidney yang in TCM, which must be evaluated by the TCM doctor in the enrolling center. For the criteria of insufficiency of spleen qi and deficiency of kidney yang in TCM, the main symptoms include weakness, atrophy, and fasciculations of the muscles. Spiritual exhaustion, shortness of breath, fear of cold or limb cooling, spontaneous sweating, and weakness of the waist and knees were considered minor symptoms. The tongue is reddish or light and the pulse is heavy and thin. Patients with at least two main symptoms and at least two minor symptoms, along with the corresponding condition of the tongue and pulse, can be diagnosed with insufficiency of spleen qi and deficiency of kidney yang in TCM.

### 2.3. Eligibility criteria

#### 2.3.1. Inclusion criteria

Patients diagnosed with clinically definite ALS, clinically probable ALS, or clinically probable-laboratory-supported ALS.Each term of the ALS Functional Rating Scale Revised (ALSFRS-R) score is no less than two points (dyspnea, orthopnea, and respiratory insufficiency must be 4 points).Forced vital capacity (FVC) is no less than 70% of the predicted value for a person’s age, sex, and height.Disease duration ≤3 years at the screening visit.TCM syndrome of insufficiency of spleen qi and deficiency of kidney yang.Aged 45–70 years, male or female.Patients who voluntarily signed an informed consent (IC) form.

#### 2.3.2. Exclusion criteria

Patients diagnosed with familial ALS.Presence of gastrostomy.The presence of other neurological diseases that mimic ALS or disturb the evaluation of its efficacy, such as cervical spondylosis myelopathy, lumbar spondylosis, and dementia.Patients with a conduction block in motor nerves or abnormalities in sensory nerves on electromyography or with lesions in images (magnetic resonance imaging or computed tomography) that might explain the clinical findings.Exposure to riluzole or edaravone within 3 months of screening. If previously exposed to riluzole or edaravone, a 3-month washout period will be required prior to screening.A spinal operation after symptom onset of ALS.Alanine aminotransferase (ALT) and/or aspartate aminotransferase (AST) exceeds 1.5 times the upper limit of normal (ULN). Serum creatinine exceeds the ULN.Any other clinically significant neurological, cardiac, pulmonary, hematological, endocrine, or psychiatric disorders.History of alcohol or drug abuse.Pregnant women or women currently breastfeeding. Women of reproductive age refuse an effective conception control from screening to 3 months after the day of the last dose.History of a known allergy to the drugs or the excipients involved in the current trial.Within 3 months prior to screening, enrollment in other clinical trials.

### 2.4. Recruitment

Recruitment was conducted by the principal investigator or sub investigators at each enrolling center. Information about the current trial was distributed through recruitment notices, which was approved by the Ethics Committee. Subjects signed the IC voluntarily only after the investigators fully explained the procedures and disclosed possible benefits, potential risks, and the contact information of the investigator of the trial.

### 2.5. Randomization

In this study, the block randomization was adopted. The randomization lists were generated by an independent statistician using SAS V9.4 and then introduced into the central randomization system (Interactive web response system, IWRS). Patients had the equal opportunity to be assigned to receive either HLSJ or riluzole randomly, with no stratification. All patients with the IC signed received a unique identification number (ID) through the IWRS at the screening visit. This number will be constant throughout the entire study. The ID list of patients was linked to the treatment code labeled on the investigational medicinal product (IMP) boxes.

### 2.6. Blinding procedures

The current trial was designed as a double-blind (participant- and investigator-blind) treatment. The similarity of HLSJ and its placebo in terms of both granules and solution status was proven in a previous study (Wu et al., 2021). Riluzole and placebo were indistinguishable in appearance and packaging. IMP is provided by the sponsor and then packaged and labeled by authorized people not participating in the observation, monitoring, and statistical analysis.

The randomization lists and parameters for randomization, such as the random seed and block length, are sealed and kept safe by the principal investigator and sponsor. A code revealing the assignment for a specific subject cannot be opened during the study unless the subject’s therapy assignment is necessary for the choice of treatment. The patient will withdraw from further participation in the study if his code is broken. One exception is that in the event of suspected unexpected serious adverse reactions (SUSAR), the Pharmacovigilance Division may unilaterally unblind a single case according to the submission requirements of the administration, with all others remaining blind. The SUSAR subject will not be considered to have dropped out.

### 2.7. Intervention and procedure

In the HLSJ group, the trial medication will be supplied as one bag of HLSJ (20 g per bag) and one tablet of placebo riluzole twice daily. In the control group, the subjects will receive one bag of placebo HLSJ and one tablet of riluzole (50 mg per tablet) twice daily. The HLSJ or placebo granule and one cup of room temperature water should be mixed and stirred vigorously, and then drunk completely within 1 h of the brew. The treatment will be performed for 48 weeks.

The trial will consist of 14 visits (V0–V13). The screening visit will be carried out within 7 days before the first dose treatment. Subsequently, the participants will be observed every 12 weeks at five site-visits, V1, V4, V7, V10, and V13. A phone call visit will be performed every 4 weeks during the interval between site visits. The detailed trial procedure and workflow are presented in Figure 1 and Table 2.

**Figure 1 fig1:**
[figure not shown]
Study workflow.

**Table 2 tab2:** Study flow chart.

	V0	V1	V2	V3	V4	V5	V6	V7	V8	V9	V10	V11	V12	V13
	-7d ~ 0d	W0	W4 ± 3d	W8 ± 3d	W12 ± 7d	W16 ± 3d	W20 ± 3d	W24 ± 7d	W28 ± 3d	W32 ± 3d	W36 ± 7d	W40 ± 3d	W44 ± 3d	W48 ± 7d
	Screening	Baseline	phone call	phone call	visit	phone call	phone call	visit	phone call	phone call	visit	phone call	phone call	visit
Patient information
Informed consent	X													
Demographics	X													
Medical history	X													
TCM syndrome differentiation	X													
Concomitant treatment history	X		X	X	X	X	X	X	X	X	X	X	X	X
Screening assessment
Pregnancy test in fertile women	X													
Neuro-electrophysiological examination	X													
Inclusion/exclusion criteria	X													
Randomization		X												
Efficacy outcomes
ALSFRS-R	X	X			X			X			X			X
ROADS		X			X			X			X			X
ALSAQ-40		X			X			X			X			X
Forced vital capacity	X	X			X			X			X			X
SSCMS		X			X			X			X			X
Endpoint event					X			X			X			X
Safety outcomes
Adverse events			X	X	X	X	X	X	X	X	X	X	X	X
Vital signs and physical examination	X	X			X			X			X			X
Laboratory tests	X				X			X			X			X
Electrocardiography	X				X			X			X			X
Others
Study treatment dispensation		X			X			X			X			
Study treatment compliance					X			X			X			X

The coronavirus disease 2019 (COVID-19) pandemic is currently ongoing. If travel restrictions prevent the subjects from site visits, phone call visits or video visits are acceptable for the evaluation of ALSFRS-R and symptom scores of Chinese medicine syndrome (SSCMS; Table 3), with the source files of the process saved. Safety laboratory tests, electrocardiograms, and pulmonary function tests can be completed at a local center according to the patient’s convenience. Photos of results will be sent to the corresponding investigator to review, evaluate, and interpret the results in time. IMP, the remaining drugs, and patient diaries will be delivered by post.

**Table 3 tab3:** The symptom scores of Chinese medicine syndrome.

The symptom scores of Chinese medicine syndrome (SSCMS)				
*Main symptoms*	*None (0)*	*Mild (2)*	*Moderate (4)*	*Severe (6)*
Weakness	None	Slightly worse than normal	Slightly inconvenient in daily life	Difficult to hold objects and walk
Atrophy	None	Mild atrophy in the first interosseous muscle, with hand function not affected	Obvious atrophy in the first interosseous muscle, with hand function significantly affected	Significant atrophy in the first interosseous muscle, difficult to hold objects
Fasciculation	None	Local and occasional	Multifocal and frequent	Diffuse and persistent
*Minor symptoms*	*None (0)*	*Mild (1)*	*Moderate (2)*	*Severe (3)*
Spiritual exhaustion	None	Feel tired about oneself	Others can feel someone tired	Too fatigue to keep talking
Shortness of breath	None	Occurs when active	Occurs after slight activity	Occurs at rest
Fear of cold or limb cooling	None	Slight	Obvious	Significant: needs more clothes and bedding
Spontaneous sweating	None	Slight and occasional, clothes keep dry	Obvious, clothes wet frequently	Significant: need to change clothes daily
Weakness of waist and knees	None	Occasional	Frequent	Too significant to walk

Total SSCMS: 0–33.

ΔSSCMS = [(SSCMS before treatment-SSCMS after treatment)/SSCMS before treatment]*100%.

Significantly effective: ΔSSCMS no less than 70%.

Effective: ΔSSCMS no less than 30%, but less than 70%.

Ineffective: ΔSSCMS less than 30%.

### 2.8. Concomitant medications

All non-IMP medications taken at the initiation of the study or given additionally during the study should be recorded as concomitant medications. It is permitted to continue treatment for other medical conditions with no effect on the evaluation of the current trial. Supportive treatments, such as nutritional management and respiratory support, are recommended according to clinical guidelines if the situation deteriorates during the study. In view of the warm nature of IMP, TCM drugs that nourish yin are permitted when patients experience night sweats or constipation. Adequate treatment is recommended in the case of adverse events. It is permitted that TCM drugs with similar indications and functions are taken continuously for no more than 1 month, with a total course of no more than 2 months. The details of any other treatment, including the reason for use, name, dosage, and duration of the drugs, should be recorded in the source documents and documented in the electronic case report form (eCRF).

Riluzole (not IMP), edaravone, gene therapy, and stem cell therapy are prohibited throughout the study.

### 2.9. Outcomes

#### 2.9.1. Primary outcome

The primary outcome was the change in ALSFRS-R scores from baseline to Week 48.

#### 2.9.2. Secondary outcomes

The secondary outcomes of the study include the following:Changes in ALSFRS-R from baseline to Week 12, 24, and 36.Changes in Rasch-Built Overall Amyotrophic Lateral Sclerosis Disability Scale (ROADS) scores from baseline to Week 12, 24, 36, and 48.Changes in the percentages of measured to predicted values of FVC from baseline to Week 12, 24, 36, and 48.Changes in 40-item Amyotrophic Lateral Sclerosis Assessment Questionnaire (ALSAQ-40) scores from baseline to Week 12, 24, 36, and 48.Changes in the SSCMS from baseline to Week 12, 24, 36, and 48, and the efficacy of Chinese medicine syndrome.The rate of endpoint events and the time to endpoint events were defined as death, tracheostomy, or permanent-assisted ventilation (>22 h daily for >14 days).

#### 2.9.3. Safety

All adverse events (AE), irrespective of their seriousness, will be collected and reported. Severity of AE is graded according to Common Terminology Criteria for Adverse Events Version 5.0. The relationship between the AE and IMP is evaluated by the investigators. Once an AE is detected, the subject should be carefully evaluated, treated in a timely manner, and followed continuously until the condition is stable. SUSAR will be promptly reported to all investigators, clinical trial institutions, and ethics committees by the sponsor. The sponsor also has a duty to report SUSAR to the Medical Products Administration and Health Administrative Department. For life-threatening events, the interval should not exceed 7 days. Other events should be reported within 15 days.

### 2.10. Statistical consideration

#### 2.10.1. Sample size calculation

The superiority test was performed for the comparison of the primary outcome in the two groups. Based on a previous real-world study of the long-term use of riluzole (Chen et al., 2016) and the consensus of the experts involved in the current study, we assumed that, for the changes of ALSFRS-R score, the adjusted mean superiority through 48 weeks between the HLSJ group and control group was 2.0 points, with a standard deviation of 4.0 points. Therefore, we needed to include 64 patients in each group (128 patients in total) to provide 80% statistical power with an alpha level of 0.05 in a two-sided test. Assuming an average dropout rate of 10%, recruitment of 144 patients will be necessary.

#### 2.10.2. Analytic populations

All randomized participants, who take at least one dose of IMP and have at least one evaluation of therapeutic efficiency post baseline, are defined as the full analysis set for the primary analysis. Patients with serious protocol deviations are further excluded in a prespecified secondary analysis of the per-protocol population. Patients receiving IMP with a safety assessment will be included in the safety analysis.

The full analysis population will be analyzed for baseline characteristics and efficacy evaluation. The secondary per-protocol analysis will be performed for efficacy assessment only, and the safety analysis will be conducted only to evaluate safety.

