#### 2.10.3. Statistical analyzes

The data analysis followed the principle of intention-to-treat (ITT). The primary outcome will be compared between the two arms using the analysis of covariance for adjusted analysis, with ALSFRS-R at baseline as the covariate in the model and HLSJ group as the fixed effect. The least squares mean (LSMEAN) and its 95% confidence interval (CI) will be measured. If the lower limit of the 95% CI of the LSMEAN difference between the HLSJ and riluzole group is greater than zero, the HLSJ group will be considered superior to the riluzole group. Intra-group changes from baseline will be tested using the Wilcoxon signed-rank test. Wilcoxon rank-sum test will be used in the test of between-group differences in changes.

A similar approach will be used to analyze the secondary outcomes. Wilcoxon rank sum test (ordered categorical data) or the Cochran–Mantel–Haenszel statistics with controlled central effects will be conducted between the two groups for categorical data. We also computed the risk difference (RD) and its 95% CI. For time-to-event data, the product-limit method will be used to calculate the quartiles and two-sided 95% CI of time to each endpoint event. The Kaplan–Meier curve will be constructed and analyzed using log-rank tests.

All safety data will be documented according to the System Organ Class and Preferred Term. Subgroup analyzes will be conducted according to clinical stratification (e.g., bulbar or limb onset). The last observation carried forward (LOCF) method will be performed to impute missing values of the primary outcome measure. Missing values for secondary outcomes and safety will not be processed with a similar approach. Once the database is locked, the statistical analysis plan will not be revised. Then, the statistical analysis will be performed using SAS V9.4. In all statistical analyzes, *p*-values <0.05 are considered statistically significant with two-sided test.

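### The full analysis set requires a post-baseline efficacy evaluation, first scheduled at Week 12, so patients who leave before then are excluded despite the ITT statement, and deaths before Week 12 may be lost from the survival analyses

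*Protocol article*

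**What the plan says.** Section 2.10.2 of the protocol article gives the membership rule, "All randomized participants, who take at least one dose of IMP and have at least one evaluation of therapeutic efficiency post baseline", and adds that these patients "are defined as the full analysis set for the primary analysis". It then sets the scope: "The full analysis population will be analyzed for baseline characteristics and efficacy evaluation". The endpoint-event outcomes (death, tracheostomy or permanent assisted ventilation) are secondary efficacy outcomes in Section 2.9.2, so they fall under the same set. Section 2.10.3 opens with "The data analysis followed the principle of intention-to-treat (ITT" and imputes missing primary-outcome values by last observation carried forward (LOCF).

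On timing, Section 2.7 says "the participants will be observed every 12 weeks at five site-visits, V1, V4, V7, V10, and V13" and "A phone call visit will be performed every 4 weeks during the interval between site visits". In Table 2 every row under efficacy outcomes (ALSFRS-R, ROADS, ALSAQ-40, FVC, SSCMS and endpoint event) has its first post-baseline mark at V4, Week 12 ± 7 days. The Week 4 and Week 8 calls carry only concomitant treatment and adverse events. The outcome list agrees: "Changes in ALSFRS-R from baseline to Week 12, 24, and 36". The COVID-19 provision lets ALSFRS-R and SSCMS be rated by phone or video but adds no time point before Week 12.

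**The concern.** Whether a patient has a post-baseline evaluation is known only after randomisation and may depend on treatment and on the course of disease. Section 2.11 lets investigators withdraw a patient for deteriorating health, serious complications, allergy or a serious adverse reaction, so loss in the first 12 weeks need not be random and need not be equal between two active regimens. LOCF does not help: these patients are outside the set and have no post-baseline score to carry forward. The article describes no analysis of all randomised patients.

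The survival outcome is the most exposed. If a death before Week 12 does not count as an evaluation, nobody in the set can die before the first assessment, and the Kaplan-Meier curve contains no deaths up to that point by construction. A patient who dies at Week 8 would appear in the safety set but in neither the survival analysis nor the baseline table.

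**Working it through.** **1. The plan's own figure.** Section 2.10.1 gives a difference of 2.0, SD 4.0, two-sided alpha 0.05, power 80%, 10% dropout and 144 patients. The normal approximation is n = 2 × 4.0² × (1.960 + 0.842)² / 2.0² = 62.8, or 63 per arm. The t-test solution is 63.8, or 64 per arm (power 0.801). Then 64 / 0.9 = 71.1, or 72 per arm and 144 in total. The stated sample size reproduces and is not in dispute.

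**2. Span without an efficacy measure.** Section 2.7 says "The treatment will be performed for 48 weeks" and Table 2 first marks efficacy at Week 12. So 12/48 = 25% of follow-up passes first, or from Week 11 to Week 13 with the window.

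**3. Patients affected.** The document gives the 10% but not its timing, so timing is an assumption.

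| Assumed timing of dropout | Calculation | Patients of 144 |
|---|---|---|
| Even over 48 weeks | 0.10 × 144 × 12/48 | 3.6 |
| Constant hazard | 144 × (1 − 0.90^(12/48)) | 3.7 (3.4 at Week 11, 4.1 at Week 13) |
| Half before Week 12 | 0.10 × 144 × 1/2 | 7.2 |

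If total dropout were 20% or 30% (also assumptions), the constant-hazard figure would be 7.8 or 12.3.

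**4. Power.** With the planned difference and SD, the t-test power is 0.846 at 72 per arm, 0.836 at 70 (four patients lost in all) and 0.825 at 68 (eight lost). The loss is minor.

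**5. Bias in ALSFRS-R.** Suppose one arm of 72 loses k more such patients than the other, and their unobserved change is D points worse than that of retained patients. That arm then looks better by about k × D / 72. D is assumed to be 5 to 15 points.

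- k = 1: 5/72 to 15/72 = 0.07 to 0.21 points, or 3% to 10% of the planned 2.0.
- k = 4: 20/72 to 60/72 = 0.28 to 0.83 points, or 14% to 42% of 2.0.

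The second line puts the whole expected loss in one arm, so it is an extreme case.

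**6. Effect on the event rate.** If an arm of 72 has x patients with an event and one who died before Week 12 is removed, its rate goes from x/72 to (x − 1)/71, a fall of (72 − x)/5112. For small x that is about 1.4 percentage points per death removed. The documents give no expected number of events, so the effect on the log-rank test cannot be sized.

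**The case against.** Four points on the other side deserve weight.

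- **Deaths.** The rule asks for an evaluation of efficacy, not an ALSFRS-R score, and Table 2 lists endpoint events under efficacy outcomes. A recorded death may therefore qualify. A reader might infer that every death before Week 12 is certainly dropped from the survival analyses; the documents do not support that certainty. Nor do they exclude it: Section 2.10.2 is silent and Table 2 first records endpoint events at Week 12. The ambiguity stands.
- **Stopping treatment.** A reader might infer that anyone who stops study drug for toxicity is excluded. That is wrong. One dose is enough, withdrawal under Section 2.11 is at the investigator's discretion, and a patient rated at Week 12 stays in. An early-termination rating would also qualify. The article mentions none, but a condensed article may leave that to the full protocol.
- **Small numbers.** Entry requires FVC of at least 70% of predicted, every ALSFRS-R item at 2 or more and the respiratory items at 4 (Section 2.3), so very early deaths should be few. A claim that the survival result would change materially would need an event count, which the documents do not give.
- **Common practice.** Sets of this kind are widely used as modified ITT, the rule is openly prespecified, and exclusions would arise under blinding. All true, but it argues for a modest grade and an accurate label. It does not make the set ITT.

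**Conclusion.** The point holds in limited form. As stated, the rule makes membership of the primary set depend on a post-randomisation event that cannot be met on schedule until about Week 12, and this conflicts with the ITT statement. Requiring a dose is a further departure from strict ITT. The expected number is about 4 of 144, or about 7 if dropout is front-loaded; both rest on the stated 10% and an assumed timing. Power is barely touched. For ALSFRS-R the bias is small unless losses are strongly one-sided. The firmer reason to act is the survival outcome, where the text leaves open whether the earliest deaths are counted.

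A reader might go further and infer that the primary ANCOVA with LOCF must give way to a longitudinal likelihood model. This point does not support that. Patients with only a baseline score add almost nothing to the treatment contrast in such a model, and it would not correct outcome-dependent early loss. The choice of primary model is a separate question.

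**What to change.** Before database lock:

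1. Run the endpoint-event rate, Kaplan-Meier and log-rank analyses on all randomised patients, as randomised, with time counted from the randomisation date. State that a death before Week 12 is an event, and censor patients who leave without an event at last contact.
2. Present baseline characteristics for all randomised patients, and report by arm the number and reasons for those without a post-baseline evaluation.
3. For ALSFRS-R, either keep the present set and call it modified ITT, removing the unqualified ITT statement, or add an all-randomised sensitivity analysis that imputes patients without post-baseline scores under stated assumptions, including unfavourable ones.

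The cost is a few sentences in the protocol or analysis plan and a small amount of extra analysis. Sample size and visit schedule are unchanged and no new data are needed. Section 2.10.3 bars revision of the analysis plan only once the database is locked. If lock has already passed, report these analyses and label them as added afterwards.
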